## Abstract

**Background:** The optimal timing of anticoagulation after stroke in patients with atrial fibrillation (AF) is unknown.

**Aim and Hypothesis:** Our primary aim is to demonstrate the safety of edoxaban initiation within 5 days of AF related stroke. Our secondary aim is to determine predictors of hemorrhagic transformation (HT) after AF related stroke. We hypothesize that the rate of radiological HT will not be increased in patients starting edoxaban within 5 days of AF related stroke, relative to those in whom initiation is delayed. We hypothesize that the risk of HT in patients treated with edoxaban can be predicted using RNA expressed in leukocytes at time of stroke.

**Methods and Design:** LASER (Lixiana Acute Stroke Evaluation Registry) is a randomized controlled trial with an associated registry (clinicaltrials.gov NCT03494530). One hundred and fifty patients with ischemic stroke and AF will undergo baseline Computed Tomography (CT) scan and will be randomized 2:1 within 5 days of symptom onset to early (≤5 days, *n* = 100) or delayed (6–14 days, *n* = 50) edoxaban initiation. Participants will undergo clinical assessment and repeat CT at 7 days and clinical assessment at 90 days.

**Study Outcomes:** The primary outcome is the rate of incident radiological HT. Secondary outcomes include symptomatic HT, recurrent ischemic stroke, recurrent sub-clinical infarcts on follow up CT, systemic hemorrhagic complication rate, National Institute of Health Stroke Scale and modified Rankin Scale at day 7 and 90, mortality within 90 days, quality of life assessments at day 90, and predictors of HT, including RNA expression by 6 pre-selected candidate genes.

**Discussion:** Event rates for both HT and recurrent ischemic events, in patients treated with early vs. delayed edoxaban initiation are unknown. The primary study endpoint of LASER is an objective performance criterion relevant to clinical decision making in patients with AF related stroke. This study will provide data required for a definitive safety/efficacy study sample size power calculation.

## Introduction

The optimal timing of anticoagulation after ischemic stroke is an area of clinical equipoise. It is clearly established that patients with atrial fibrillation (AF) who develop ischemic stroke are at high risk for recurrence and require long-term anticoagulation. Previous studies have reported that starting older anticoagulants within 48 h after acute ischemic stroke is associated with a reduction in the rate of recurrent ischemic events, but that is offset by an increased risk of hemorrhagic transformation (HT) (1–3). More recently, four direct oral anticoagulation (DOACs) have shown a lower risk of intracranial hemorrhagic complications compared to older anticoagulants, and they are now the standard of care for long-term stroke prevention in non-valvular AF (4–7). In the pivotal phase III DOAC trials, patients were not eligible for randomization as early as 7 days and up to 30 days after ischemic stroke. Current stroke guidelines are inconsistent regarding the timing of DOAC initiation and recommendations are based on expert opinion only (8–10).

Edoxaban is one of the DOACs approved for the prevention of ischemic stroke in patients with AF (7). Patients within 30 days of ischemic stroke were excluded from the Effective Anticoagulation with Factor Xa Next Generation in Atrial Fibrillation - Thrombolysis in Myocardial Infarction 48 (ENGAGE AF-TIMI 48) trial. As with other DOACs, there are no randomized data related to the use of edoxaban early after ischemic stroke. The optimal timing of DOAC initiation is unknown and a clinical problem commonly encountered by stroke physicians. Even less is understood about the timing of anticoagulation after HT, asymptomatic or otherwise, has occurred.

Symptomatic HT remains difficult to predict. Although clinical severity and infarct volume appear to increase HT risk (11, 12), the association is highly inconsistent. Novel biomarkers would be useful in determining DOAC timing. Preliminary data suggest the risk of HT in patients with stroke can be stratified by RNA expressed in circulating leukocytes within 3 h of stroke onset. A panel of 6 genes associated with subsequent HT has been identified (13, 14).

The primary aim of the Lixiana Acute Stroke Evaluation Registry (LASER) is to demonstrate the safety of edoxaban initiation within 5 days of AF related stroke. Secondary aims include identification of clinical, imaging and RNA transcript predictors of HT. We hypothesize that edoxaban initiation within 5 days of ischemic stroke will not be associated with increased HT rates, relative to patients in whom anticoagulation is delayed. Serial imaging using Computed Tomography (CT) will be utilized to determine the rate of radiological HT after edoxaban initiation. Incident radiological HT rates will be assessed as objective performance criteria for the safety of early vs. delayed edoxaban initiation (15–17). We also hypothesize that RNA expressed in leukocytes at time of stroke can stratify risk of HT in patients treated with edoxaban. We will assess the rate of recurrent ischemic stroke, but recognize any differences between groups will be hypothesis generating only due to the small trial sample size.

## Methods

### Study Design

LASER is a randomized controlled, parallel-group, two-arm, assessor-blinded trial with an associated registry (clinicaltrials.gov NCT03494530). Patients with previously known or newly diagnosed AF-related ischemic stroke will be randomized 2:1 to early (≤5 days) or delayed (6–14 days) edoxaban initiation (Figure 1). Ischemic stroke will be defined as evidence of acute focal cerebral infarction confirmed on CT/MRI and/or focal hypoperfusion/vessel occlusion on multimodal CT, or by sudden focal and objective neurological deficits (i.e., NIHSS ≥ 1) of presumed ischemic origin persisting > 24 h. Informed consent will be obtained from the patient or substitute decision maker in all cases prior to enrolment. The research protocol has been approved by our local Human Research Ethics Board.

**Figure 1 F1:**
[figure not shown]
Randomized trial and registry schema. PH, parenchymal hematoma; CT, computed tomography; HT, hemorrhagic transformation. *All stroke severities, infarction sizes and HT (Hemorrhagic infarction type 1 and Hemorrhagic infarction type 2) are eligible for randomization.

### Patient Population

One hundred fifty patients from a Comprehensive Canadian Stroke Center will be enrolled. Eligible patients will be randomized within 5 days of symptom onset after baseline CT. Inclusion and exclusion criteria are shown in Table 1.

**Table 1 T1:** Study inclusion and exclusion criteria.

**Inclusion criteria**
Male or female patients
≥18 years of age
Ischemic stroke, diagnose and enroll ≤ 5 days from symptom onset^*^
AF (paroxysmal or persistent), confirmed with ECG/Holter monitor, or by history (clinical documentation of previous AF must be provided)
Informed consent
**Exclusion criteria**
Acute or chronic renal failure, defined as eCrCl <30 ml/min (Cockcroft Gault formula)
Known hypersensitivity to edoxaban
Any significant ongoing systemic bleeding risk, or recent major surgery
Recent past history or clinical presentation of ICH, SAH, AVM, aneurysm, or cerebral neoplasm
Hereditary or acquired haemorrhagic diathesis
Stroke mimics
HT with a grade of PH1 or PH2 on baseline or screening CT†
Any condition that, in the judgment of the investigator(s), could impose hazards to the patient if study therapy is initiated

* *Ischemic stroke is defined as evidence of acute focal cerebral infarction confirmed on CT/MRI and/or focal hypoperfusion/vessel occlusion on multimodal imaging, or by sudden focal and objective neurological deficits (i.e., NIHSS ≥ 1) of presumed ischemic origin persisting > 24 h*.

† *Eligible for registry*.

*AF, atrial fibrillation; ECG, electrocardiography; eCrCl, estimated creatinine clearance; ICH, intracerebral hemorrhage; SAH, subarachnoid hemorrhage; AVM, arteriovenous malformation; HT, hemorrhagic transformation; PH, parenchymal hemorrhage; CT, computed tomography*.

Patients with spontaneous parenchymal hemorrhage (PH) [European Cooperative Acute Stroke Study (ECASS)] grade PH1 or PH2 on the baseline CT will not be eligible for randomization (18). These patients will be included in the registry portion of LASER and follow-up will be identical to that in the trial. The timing of edoxaban initiation in these patients will be at the discretion of the treating physician.

### Randomization

Eligible patients will be randomized 2:1 following open label simple randomization procedure to early (≤ 5 days) or delayed (6–14 days) edoxaban initiation via a centralized web-based randomization process, Research Electronic Data Capture (REDCap, Vanderbilt university) (19, 20). After randomization to early or delayed arms, the decision to time the edoxaban initiation within the specific arm will be at the treating physician's discretion.

The rationale for the specific timing of treatment, within the randomization window, will also be recorded by surveying the treating physician in each case.

### Treatment

Randomized patients will be treated with edoxaban 60 mg once daily. The edoxaban dose will be reduced to 30 mg once daily if any of the following characteristics are present at the time of randomization or during the study: estimated creatinine clearance (CrCl) of 30–50 ml per min using Cockcroft-Gault Equation or body weight ≤ 60 kg. Prior to edoxaban initiation, all patients will be treated as per the clinical standard of care using antiplatelet(s) and anticoagulation for deep venous thrombosis (DVT) prophylaxis. Any antithrombotic therapy prior to randomization will be recorded.

### Clinical Assessment

All randomized patients will be followed for 90 days after edoxaban initiation. A National Institute of Health Stroke Scale (NIHSS) score will be assessed at baseline, 7 and 90 days after edoxaban initiation. Functional outcome will be assessed with a modified Rankin Scale (mRS) score at baseline, 7 and 90 days after edoxaban initiation. Montreal Cognitive Assessment (MoCA) will be performed at baseline, and day 90 after edoxaban initiation. Functional outcome at 90 days will be dichotomized as favorable (mRS score 0–2) and unfavorable (mRS score 3–6). Quality of life will be assessed with the EuroQol-5 Dimension (EQ-5D) and Visual Analog Scale (VAS) at day 90.

### Standardized Image Acquisition and Central Analysis

In addition to diagnostic imaging, all patients will have a baseline CT prior to randomization and follow up CT 7 ± 2 days after edoxaban initiation. Therefore, all patients will have a minimum of two scans (diagnostic and pre-randomization). In the event of clinical deterioration, CT scans will be repeated. In patients treated with thrombolysis and/or endovascular thrombectomy, a 24-h post-treatment CT will be used as the baseline study prior to randomization.

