### Imaging Protocol

The original LASER protocol included MRI acquisition in all patients. Following diagnostic CT, all patients were to undergo MRI including diffusion-weighted imaging (DWI to assess the acute infarct volume), Fluid Attenuated Inverse Recovery (FLAIR to assess chronic infarct and white matter ischemic change volumes) and susceptibility weighted imaging (SWI to assess for acute HT and chronic cerebral microbleeds) prior to randomization.

Shortly after trial initiation, however, COVID-19 restrictions limited access to research MRI protocols. The protocol was therefore amended and both baseline and day 7 imaging will be performed using non-contast, axial CT.

All CT scans will be assessed by two independent raters, blinded to treatment group, for the presence, number and total volume of regions with infarction. Infarct volumes will be measured using planimetric techniques (Analyze 11.0, Biomedical Imaging Resource, Mayo Clinic) (21). Any HT, as well as other intracranial hemorrhage, seen at baseline and day 7 will be graded using the Heidelberg Bleeding Classification (HBC) (22). Incident HT seen on follow-up CT scan is defined as new or progressive HT. Progressive HT will be defined as any increase in the severity grade between the baseline and follow-up scan. Two raters will rate the HT using the Heidelberg criteria.

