## Study Outcomes

The primary study endpoint is the rate of incident (new or progressive) radiological HT. The secondary endpoint is the rate of symptomatic HT, defined as intracerebral hemorrhage within and beyond infarcted brain tissue with PH > 1/3 the volume of the ischemic infarct (Class 2 in HBC) associated with clinical deterioration (worsening of NIHSS score by ≥4 points) within 30 days of treatment initiation (18, 22). Other secondary endpoints are recurrent ischemic stroke within 90 days of randomization, recurrent sub-clinical infarcts on follow up CT at 7 ± 2 days post edoxaban initiation, systemic hemorrhagic complication rate within 90 days of randomization, NIHSS at day 7 and 90, mRS score at day 7 and 90, favorable mRS at day 90, and mortality within 90 days, quality of life at 90 days assessed by EQ-5D and VAS, and ability of leukocyte RNA to predict HT.

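### The primary follow-up CT is timed from edoxaban start while the reference CT precedes randomisation, so the arms are compared over unequal windows and their difference can only be descriptive

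*Protocol article*

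**What the plan says.** All places are in the protocol article.

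- **Allocation (Study Design):** patients are "randomized 2:1 to early (≤5 days) or delayed (6–14 days) edoxaban initiation". Under Randomization, "the decision to time the edoxaban initiation within the specific arm will be at the treating physician's discretion".
- **Baseline (Patient Population):** "Eligible patients will be randomized within 5 days of symptom onset after baseline CT". This holds for both arms.
- **Scans (Standardized Image Acquisition and Central Analysis):** "all patients will have a baseline CT prior to randomization and follow up CT 7 ± 2 days after edoxaban initiation". Any other CT is prompted by clinical deterioration.
- **Endpoint (Imaging Protocol, Study Outcomes):** "Incident HT seen on follow-up CT scan is defined as new or progressive HT", with progression meaning a higher grade than at baseline. "The primary study endpoint is the rate of incident (new or progressive) radiological HT". No window from onset or randomisation is attached, although recurrent stroke and systemic haemorrhage are counted from randomisation.
- **Analysis (Statistical Analysis):** rates with 95% CIs by arm under intention-to-treat, and Fisher's exact test on the unadjusted difference. Adjustment is reserved for baseline imbalance in NIHSS, infarct volume or HT.
- **Hypothesis (Abstract, Introduction):** HT is not increased by early start relative to delayed start.

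**The concern.** The reference scan is tied to stroke onset and randomisation, but the outcome scan is tied to drug start. Because drug start is the randomised factor, the arm determines how long a patient is observed between the two scans and how old the infarct is when it is read. Randomisation cannot balance a quantity that the assignment itself produces.

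The endpoint is also not confined to HT on drug. A delayed patient who bleeds into the infarct after the baseline CT but before the first edoxaban dose is scored as an incident case.

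What is at stake is the comparative statement. A lower or equal HT rate in the early arm could reflect a safe early start, a shorter observation window, or both. The planned test cannot tell these apart.

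**Working it through.** **1. The plan's own figures.** Sample Size Estimates gives 3% (0.6–8.5%) for n = 100 and 4% (0.5–13.7%) for n = 50. Exact (Clopper-Pearson) limits are 0.62–8.52% for 3/100 and 0.49–13.71% for 2/50. Both reproduce, and the timing issue does not affect them.

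**2. Windows, from the plan's limits.** Edoxaban starts on day 0–5 (early) or 6–14 (delayed). The scan follows 5–9 days later. The baseline CT is on day 0–5.

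| | Early | Delayed |
|---|---|---|
| Stroke day at scan | 0+5 to 5+9 = 5–14 | 6+5 to 14+9 = 11–23 |
| Baseline-to-scan interval, days | 0+5 to 5+9 = 5–14 | (6−5)+5 to (14−0)+9 = 6–23 |

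Stroke age at scan overlaps only on days 11–14. If start days are uniform within the windows and the baseline CT is uniform on day 0.5–5 (both assumptions), the mean interval is about 8.1 days in the early arm and 14.3 in the delayed arm.

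**3. Possible size with no drug effect.** The documents give no HT hazard over time, so I assume shapes and show the range. Take a baseline CT on day 2, starts on days 3 and 10, and scans 7 days later, on days 10 and 17. The intervals are 8 and 15 days. Set the early rate at 3%, so its cumulative hazard is −ln(0.97) = 0.03046. The delayed rate is 1 − exp(−0.03046 × R), where R is the ratio of cumulative hazards.

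- Constant hazard: R = 15/8 = 1.875, delayed rate 5.6%.
- Hazard decaying from onset with time constant τ: R = (e^(−2/τ) − e^(−17/τ)) / (e^(−2/τ) − e^(−10/τ)).
  - τ = 14 days: R = 1.51, delayed rate 4.5%.
  - τ = 7 days: R = 1.30, delayed rate 3.9%.
  - τ = 3 days: R = 1.07, delayed rate 3.2%.

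The range is 3.2% to 5.6%. A simulation with the uniform start and baseline days of step 2 gives 3.2% to 5.2%, a rate ratio of 1.06 to 1.73.

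**4. Sign.** Step 3 assumes that HT, once present, stays visible. HT that fades on CT before a later scan would be missed more often in the delayed arm, which pushes the other way. The documents do not settle which dominates.

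**5. What the planned analysis could show.** Even at the top of the range (3.0% v 5.55%, n = 100 and 50), the approximate 95% CI for the 2.6-point difference runs from −4.6 to +9.7 points, and Fisher's test would reject in about 11% of trials. The artefact is unlikely to produce a significant result. The risk lies in reading the observed rates as reassurance.

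**The case against.** The best defence is that timing the scan from drug start is a reasonable safety choice: both arms have the same time on edoxaban when imaged. A common clock from randomisation would lose that. If 7 ± 2 days were counted from randomisation, some delayed patients would be scanned before any edoxaban; a later common scan could miss early-arm HT that has faded. This stands, and it is why moving the scan is not required here. It does not rescue the comparison, because the reference scan is still the pre-randomisation one.

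A second defence is that the trial is sized for precision within each arm, as Sample Size Estimates says. That also stands: each rate and its CI validly describes its own window. But the Abstract and Introduction state a between-arm hypothesis, Statistical Analysis tests the difference, and the sample-size section claims enough precision to demonstrate safety.

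Two stronger readings are tempting and unsupported.

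- A reader might set the artefact against a planned 1-point difference (3% v 4%). The plan assumes no difference. It says no such data exist, and the two percentages are illustrative counts for exact intervals.
- A reader might infer that infarct age on CT unblinds the raters. The article says they are blinded, and nothing shows that they see dates or can deduce the arm.

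**Conclusion.** The point holds as a limit on what the arm comparison can conclude. Unequal windows follow directly from the plan's text, and neither the analysis nor the Limitations section addresses them. The consequence in percentage points cannot be derived: about 3.2% to 5.6% in the delayed arm against 3% in the early arm, given no drug effect, the assumed hazards and persistent HT. The upper end needs a constant hazard. If spontaneous HT is concentrated in the first days, the artefact is small.

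A reader might conclude that the design favours early start. That follows only if HT accumulates on CT; fading HT would reverse it.

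The day-7 NIHSS ("score will be assessed at baseline, 7 and 90 days after edoxaban initiation") and mRS share the anchor. They are secondary, and Limitations already says the trial is not powered for clinical outcomes.

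**What to change.** 1. In Sample Size Estimates and Statistical Analysis, state that the two rates describe HT from baseline to about 7 days after edoxaban start over unequal windows. State also that their difference is descriptive and does not by itself show that early start leaves HT unincreased.
2. Add scan timing to Limitations.
3. Define as incident any new or progressive HT on any post-randomisation scan, including scans done for deterioration.
4. Report the baseline-to-scan interval by arm. As a sensitivity analysis from recorded scan dates, give HT per day of that interval, with its constant-hazard assumption stated. If the hazard decays, this over-corrects: in the example with τ = 3 days and no drug effect, the delayed-to-early ratio per day is 1.07/1.875 = 0.57. It should therefore sit beside the crude comparison and not replace it.

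**Cost.** No extra scans or patients are needed. The stated conclusion becomes less favourable, and the sensitivity analysis will be imprecise: the illustrative counts total 3 + 2 = 5 events. For the same reason, interval-censored modelling with one scheduled follow-up scan per patient is barely workable.

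**Optional.** A common scan time from randomisation would equalise the windows at the price of unequal time on drug. Changing it during enrolment would also mix two endpoint definitions.

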### Imaging Protocol

The original LASER protocol included MRI acquisition in all patients. Following diagnostic CT, all patients were to undergo MRI including diffusion-weighted imaging (DWI to assess the acute infarct volume), Fluid Attenuated Inverse Recovery (FLAIR to assess chronic infarct and white matter ischemic change volumes) and susceptibility weighted imaging (SWI to assess for acute HT and chronic cerebral microbleeds) prior to randomization.

Shortly after trial initiation, however, COVID-19 restrictions limited access to research MRI protocols. The protocol was therefore amended and both baseline and day 7 imaging will be performed using non-contast, axial CT.

All CT scans will be assessed by two independent raters, blinded to treatment group, for the presence, number and total volume of regions with infarction. Infarct volumes will be measured using planimetric techniques (Analyze 11.0, Biomedical Imaging Resource, Mayo Clinic) (21). Any HT, as well as other intracranial hemorrhage, seen at baseline and day 7 will be graded using the Heidelberg Bleeding Classification (HBC) (22). Incident HT seen on follow-up CT scan is defined as new or progressive HT. Progressive HT will be defined as any increase in the severity grade between the baseline and follow-up scan. Two raters will rate the HT using the Heidelberg criteria.

### RNA Analysis

A blood sample will be drawn into a PAXgene tube for RNA analysis at the time of the baseline CT. RNA will be isolated and measured by RNA sequencing and reverse transcription polymerase chain reaction (RT-PCR). Genes different between patients who develop HT compared to those without HT will be identified by analysis of variance adjusted for covariates as previously described (13, 14). A prediction model will be developed using the identified genes. The ability of the developed gene model to predict HT will be compared to other factors associated with HT including age, stroke severity, infarct volume.

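### The RNA hypothesis concerns expression at the time of stroke, but blood is drawn at the baseline CT, up to 5 days later and in some patients after a bleed, so the hypothesis, outcome and covariates should be aligned with that sample

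*Protocol article*

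**What the plan says.** **Hypothesis.** The Abstract states that "the risk of HT in patients treated with edoxaban can be predicted using RNA expressed in leukocytes at time of stroke", and the aims at the end of the Introduction repeat it: "RNA expressed in leukocytes at time of stroke can stratify risk of HT in patients treated with edoxaban".

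**Basis.** The Introduction rests this on preliminary data in which HT risk was "stratified by RNA expressed in circulating leukocytes within 3 h of stroke onset" and from which a six-gene panel came.

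**Sample.** RNA Analysis states: "A blood sample will be drawn into a PAXgene tube for RNA analysis at the time of the baseline CT". On the timing of that scan, Patient Population says: "Eligible patients will be randomized within 5 days of symptom onset after baseline CT". Standardized Image Acquisition and Central Analysis makes the baseline CT additional to diagnostic imaging. After thrombolysis or thrombectomy, the CT 24 h after treatment serves as baseline.

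**Baseline bleeding.** The legend to Figure 1 states: "All stroke severities, infarction sizes and HT (Hemorrhagic infarction type 1 and Hemorrhagic infarction type 2) are eligible for randomization". Under Imaging Protocol, incident HT is new or progressive HT, and progression is any rise in grade between baseline and follow-up.

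**Analysis.** RNA Analysis states: "Genes different between patients who develop HT compared to those without HT will be identified by analysis of variance", adjusted for covariates as in two cited sources. The gene model is then compared with clinical factors. The two lists given, in RNA Analysis and Statistical Analysis, name age, stroke severity, infarct volume, blood pressure, glucose and thrombolysis. Neither names onset-to-draw time or baseline HT. Baseline HT appears in Statistical Analysis only as a reason to adjust the crude primary rates if it is imbalanced.

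**The concern.** The hypothesis and the sampling rule describe different measurements. Expression within hours of onset and expression at a scan taken between day 0 and day 5 need not carry the same information about later bleeding. A result from the second would be reported under a hypothesis about the first.

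Two features of the later sample affect interpretation:

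- **Draw time is linked to treatment.** It is set by the 24-h scan in reperfused patients and is free up to day 5 in the rest. Thrombolysis is one of the article's own HT risk factors, so a gene that changes with time since onset could be associated with HT through reperfusion.
- **Some samples follow a bleed.** In patients with HI1 or HI2 on the baseline CT, expression may reflect the hemorrhage already there. If those patients are also more likely to be counted as incident cases through progression, a marker of existing HT would look like a predictor.

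The Discussion gives the purpose of the biomarker as guiding anticoagulation timing. A marker that only restates what the baseline CT already shows would not serve that purpose.

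**Working it through.** **1. Sampling time**

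| Item | Time | Source |
|---|---|---|
| Preliminary data | up to 3 h from onset | Introduction |
| Hypothesis | at the time of the stroke | Abstract; Introduction |
| Latest possible draw | 5 × 24 = 120 h from onset | Patient Population; RNA Analysis |
| Draw in reperfused patients | about 24 h after treatment, so at least about 24 h from onset | Standardized Image Acquisition and Central Analysis; RNA Analysis |

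Ratio of upper limits: 120 / 3 = 40. For reperfused patients: 24 / 3 = 8 or more, so no such patient can match the 3-h window. These are ratios of limits. The article gives no distribution of draw times.

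**2. What the RNA contrast does with each type of patient**, if its outcome is incident HT as defined under Imaging Protocol:

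| Baseline CT | Follow-up CT | Group | Sample relative to first bleed |
|---|---|---|---|
| No HT | No HT | comparator | no bleed |
| No HT | New HT | case | before |
| HI1 or HI2 | Grade not increased | comparator | after |
| HI1 or HI2 | Grade increased | case | after |

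Only the second row is prediction of HT from a sample taken before any bleed. The fourth row brings a post-bleed sample into the case group. The third brings post-bleed samples into the comparators, which would pull the other way. The net direction depends on how often baseline HI progresses compared with how often HT appears in patients free of it, and the article gives neither rate. RNA Analysis does not say which group the third row belongs to.

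**3. How many cases there are**

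Sample Size Estimates gives 3% (0.6–8.5%) of 100 and 4% (0.5–13.7%) of 50. The exact (Clopper-Pearson) limits are the 2.5% quantile of Beta(x, n − x + 1) and the 97.5% quantile of Beta(x + 1, n − x):

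- x = 3, n = 100: 0.62% to 8.52%
- x = 2, n = 50: 0.49% to 13.71%

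Both reproduce the printed intervals, so the plan corresponds to 3 + 2 = 5 events. At the 13% quoted for MRI-based studies it would be 0.13 × 150 = 19.5, about 20, but imaging is now CT only. With 5 cases, one patient from the fourth row is 1/5 = 20% of the case group.

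**4. How many samples could follow a bleed**

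The prevalence of baseline HI is not given. Assumed range, in 150 patients:

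| Assumed prevalence | Patients with HI at the draw |
|---|---|
| 3% | 4.5 |
| 5% | 7.5 |
| 10% | 15 |
| 13% | 19.5 |
| 20% | 30 |

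Over this range the number sampled after a bleed is about equal to, or larger than, the 5 planned events. This does not say how many would be counted as cases. It shows only that baseline HT status cannot be presumed negligible in a contrast with so few cases.

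**The case against.** The strongest reply is that patients who develop HT most naturally means incident HT, the trial's own endpoint, measured after the sample. On that reading stable baseline HI is not a case, and only progressors carry a post-bleed sample into the case group. That stands. It narrows the problem to the fourth row of the table and the makeup of the comparators, but does not remove it.

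Four stronger readings are tempting, and the article does not support them:

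- **That the trial cannot test its hypothesis at all.** Patients who are not reperfused may have an early baseline CT, and an early-drawn subset could bear on the hypothesis.
- **That already-bled patients would outnumber true cases by 1.5:1 to 6:1** (7.5 / 5 to 30 / 5). This needs an assumed prevalence of 5–20% and also the counting of every baseline HI as a case. Nothing in the article states that pooling.
- **That the covariates certainly omit draw time.** They are defined by two cited sources that are not at hand, and a full covariate list may properly sit in the full protocol or analysis plan. The point here rests on the mismatch that the article states, not on the absence of a list.
- **That the earlier panel would fail to replicate.** The plan also identifies genes anew and builds its own model, and what happens at later draw times is unknown.

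It can also be said that prediction at the pre-randomization scan, with HI patients included, is a coherent question. That is so, and it is a reason not to make an HT-free subset the main analysis. It is not, however, the question the hypothesis states. Finally, the sample precedes randomization and so precedes study edoxaban in randomized patients; no drug effect on expression is at issue.

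**Conclusion.** The concern holds in this form. The article's hypothesis is about RNA at the time of stroke, while its design measures RNA at the pre-randomization CT, as late as 120 h after onset and not before about 24 h in reperfused patients. Draw time is thereby linked to reperfusion treatment. Because HI1 and HI2 are eligible, some samples follow an existing bleed, and a marker of existing HT could be taken for a predictor.

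The mismatch in timing and the eligibility of HI1 and HI2 come straight from the text and need no assumption. That confounding by draw time or baseline HT would be material is a possibility: the planned case group is about 5, so it is sensitive to single patients. Neither the size nor the direction of any bias can be computed without the prevalence of baseline HI, its progression rate and the distribution of draw times.

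This affects a secondary aim. It does not touch the primary endpoint, the randomization or the safety estimates. It is worth correcting because it changes what the biomarker analysis may conclude.

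**What to change.** 1. In the Abstract and the aims, and in any later conclusion, reword the RNA hypothesis to leukocyte RNA at the baseline CT, within 5 days of onset.
2. In RNA Analysis, state that the outcome is incident HT on the follow-up CT as defined under Imaging Protocol, so that stable baseline HI is not a case.
3. In RNA Analysis and Statistical Analysis, include onset-to-draw time and baseline HT status as covariates in the gene analysis and in the prediction model. The question then becomes whether RNA adds to what the baseline scan shows.
4. Add two sensitivity analyses: patients with no HT on the baseline CT, and the earliest-drawn samples.

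**Cost.** No change to treatment, visits or sampling is needed. Baseline HT grade is already planned. The article does not say that draw time is recorded; if it is not, the time of the baseline CT can stand in, since the draw is tied to it. The hypothesis becomes narrower. With about 5 planned events, the adjusted model and both sensitivity analyses will be imprecise, and the analysis without baseline HT loses the progressive cases. They should be reported as descriptive checks on the main result.
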